### Outcome measures

The primary outcome measure is the change from week 0 to week 5 in subjective sleep efficiency derived from the sleep diary. Secondary subjective sleep estimates include difficulties falling asleep, difficulties maintaining sleep, early morning awakening and non-restorative sleep. A secondary outcome regarding daytime consequences is the average rating of evening diary ratings on eighteen major daytime functioning complaints. Ancillary analyses on persistence of treatment use the same variables obtained in week 10.

Actigraphically estimated objective sleep parameters (sleep efficiency, sleep onset latency, sleep duration, wake after sleep onset, and the average durations of uninterrupted periods of sleep and wakefulness) are secondary outcome measures meant to complement the subjective evaluations. These are calculated from the ActiWatch Spectrum recordings using the Respironics Actiware software (version 5.71.0, Philips Respironics, Murrysville, PA, USA). Given the variability in subjective [88] and objective [89] sleep estimates, they will be assessed for 7 subsequent days at each assessment. Additional questionnaires, assessed in weeks 0, 5 and 10, will provide secondary outcome measures (see the list above). Specifically, the direct and indirect medical costs (TiC-P) will be included.

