#### Treatment effects and moderation estimates

Mixed effect models will be applied to estimate all time by treatment effects, time by treatment interaction effects and effect moderation by the individual’s insomnia subtype probabilities. For each outcome measure, all effects will be estimated simultaneously in one single linear regression equation. The primary outcome measure of sleep efficiency will be illustrated below. The diary and actigraphy based outcome measures have a two-level hierarchical data-structure: repeated measures of 14 diary inputs *i* across T0 and T1 are nested within subjects *j*. The 14*160 = 2,240 data points can be used to estimate simultaneously all effects ß using the following mixed effect model:$$ \begin{array}{l}\mathrm{S}{\mathrm{E}}_{\mathrm{ij}}\kern0.5em =\kern0.5em {\mathrm{\ss}}_{0\mathrm{i}\mathrm{j}}\kern0.5em +\kern0.5em {\mathrm{\ss}}_1*{\mathrm{Time}}_{\mathrm{ij}}\kern0.5em +\kern0.5em {\mathrm{\ss}}_2*\mathrm{C}\mathrm{B}\mathrm{T}\hbox{-} {\mathrm{I}}_{\mathrm{j}}\kern0.5em +\kern0.5em {\mathrm{\ss}}_3*\mathrm{B}{\mathrm{L}}_{\mathrm{j}}\kern0.5em +\kern0.5em {\mathrm{\ss}}_4*\mathrm{P}{\mathrm{A}}_{\mathrm{j}}\kern0.5em +\kern0.5em {\mathrm{\ss}}_5*\mathrm{B}{\mathrm{W}}_{\mathrm{j}}\kern0.5em +\kern0.5em {\mathrm{\ss}}_6*\mathrm{IS}{\mathrm{P}}_{\mathrm{j}}\kern0.5em +\kern0.5em {\mathrm{\ss}}_7*\mathrm{T}\mathrm{i}\mathrm{m}{\mathrm{e}}_{\mathrm{ij}}*\mathrm{IS}{\mathrm{P}}_{\mathrm{j}}+\\ {}\kern0.5em {\mathbf{\ss}}_{\mathbf{8}}*\mathbf{C}\mathbf{B}\mathbf{T}\hbox{-} {\mathbf{I}}_{\mathbf{j}}*\mathbf{T}\mathbf{i}\mathbf{m}{\mathbf{e}}_{\mathbf{ij}}\kern0.5em +\kern0.5em {\mathrm{\ss}}_9*\mathrm{C}\mathrm{B}\mathrm{T}\hbox{-} \mathrm{I}*\mathrm{IS}{\mathrm{P}}_{\mathrm{j}}\kern0.5em +\kern0.5em {\mathbf{\ss}}_{\mathbf{10}}*\mathbf{C}\mathbf{B}\mathbf{T}\mathbf{\hbox{-} }{\mathbf{I}}_{\mathbf{j}}*\mathbf{T}\mathbf{i}\mathbf{m}{\mathbf{e}}_{\mathbf{ij}}*\mathbf{I}\mathbf{S}\mathbf{P}+\\ {}\kern0.5em {\mathbf{\ss}}_{\mathbf{11}}*\mathbf{B}{\mathbf{L}}_{\mathbf{j}}*\mathbf{T}\mathbf{i}\mathbf{m}{\mathbf{e}}_{\mathbf{ij}}\kern0.5em +\kern0.5em {\mathrm{\ss}}_{12}*\mathrm{B}\mathrm{L}*\mathrm{IS}{\mathrm{P}}_{\mathrm{j}}\kern0.5em +\kern0.5em {\mathbf{\ss}}_{\mathbf{13}}*\mathbf{B}{\mathbf{L}}_{\mathbf{j}}*\mathbf{T}\mathbf{i}\mathbf{m}{\mathbf{e}}_{\mathbf{ij}}*\mathbf{I}\mathbf{S}{\mathbf{P}}_{\mathbf{j}}+\\ {}\kern0.5em {\mathbf{\ss}}_{\mathbf{14}}*\mathbf{P}{\mathbf{A}}_{\mathbf{j}}*\mathbf{T}\mathbf{i}\mathbf{m}{\mathbf{e}}_{\mathbf{ij}}\kern0.5em +\kern0.5em {\mathrm{\ss}}_{15}*\mathrm{P}\mathrm{A}*\mathrm{IS}{\mathrm{P}}_{\mathrm{j}}\kern0.5em +\kern0.5em {\mathbf{\ss}}_{\mathbf{16}}*\mathbf{P}{\mathbf{A}}_{\mathbf{j}}*\mathbf{T}\mathbf{i}\mathbf{m}{\mathbf{e}}_{\mathbf{ij}}*\mathbf{I}\mathbf{S}{\mathbf{P}}_{\mathbf{j}}+\\ {}\kern0.5em {\mathbf{\ss}}_{\mathbf{17}}*\mathbf{B}{\mathbf{W}}_{\mathbf{j}}*\mathbf{T}\mathbf{i}\mathbf{m}{\mathbf{e}}_{\mathbf{ij}}\kern0.5em +\kern0.5em {\mathrm{\ss}}_{18}*\mathrm{B}\mathrm{W}*\mathrm{IS}{\mathrm{P}}_{\mathrm{j}}\kern0.5em +\kern0.5em {\mathbf{\ss}}_{\mathbf{19}}*\mathbf{B}{\mathbf{W}}_{\mathbf{j}}*\mathbf{T}\mathbf{i}\mathbf{m}{\mathbf{e}}_{\mathbf{ij}}*\mathbf{I}\mathbf{S}{\mathbf{P}}_{\mathbf{j}}+\\ {}\kern0.5em {\mathrm{\ss}}_{20}*\mathrm{C}\mathrm{B}\mathrm{T}\hbox{-} {\mathrm{I}}_{\mathrm{j}}*\mathrm{B}{\mathrm{L}}_{\mathrm{j}}\kern0.5em +\kern0.5em {\mathbf{\ss}}_{\mathbf{21}}*\mathbf{C}\mathbf{B}\mathbf{T}\mathbf{\hbox{-} }{\mathbf{I}}_{\mathbf{j}}*\mathbf{B}{\mathbf{L}}_{\mathbf{j}}*\mathbf{T}\mathbf{i}\mathbf{m}{\mathbf{e}}_{\mathbf{ij}}\kern0.5em +\kern0.5em {\mathrm{\ss}}_{22}*\mathrm{C}\mathrm{B}\mathrm{T}\hbox{-} {\mathrm{I}}_{\mathrm{j}}*\mathrm{B}{\mathrm{L}}_{\mathrm{j}}*\mathrm{IS}{\mathrm{P}}_{\mathrm{j}}\kern0.5em +\kern0.5em {\mathbf{\ss}}_{\mathbf{23}}*\mathbf{C}\mathbf{B}\mathbf{T}\hbox{-} \\ {}\kern0.5em {\mathbf{I}}_{\mathbf{j}}*\mathbf{B}{\mathbf{L}}_{\mathbf{j}}*\mathbf{T}\mathbf{i}\mathbf{m}{\mathbf{e}}_{\mathbf{ij}}*\mathbf{I}\mathbf{S}\mathbf{P}+\\ {}\kern0.5em {\mathrm{\ss}}_{24}*\mathrm{C}\mathrm{B}\mathrm{T}\hbox{-} {\mathrm{I}}_{\mathrm{j}}*\mathrm{P}{\mathrm{A}}_{\mathrm{j}}\kern0.5em +\kern0.5em {\mathbf{\ss}}_{\mathbf{25}}*\mathbf{C}\mathbf{B}\mathbf{T}\mathbf{\hbox{-} }{\mathbf{I}}_{\mathbf{j}}*\mathbf{P}{\mathbf{A}}_{\mathbf{j}}*\mathbf{T}\mathbf{i}\mathbf{m}{\mathbf{e}}_{\mathbf{ij}}\kern0.5em +\kern0.5em {\mathrm{\ss}}_{26}*\mathrm{C}\mathrm{B}\mathrm{T}\hbox{-} {\mathrm{I}}_{\mathrm{j}}*\mathrm{P}{\mathrm{A}}_{\mathrm{j}}*\mathrm{IS}{\mathrm{P}}_{\mathrm{j}}\kern0.5em +\kern0.5em {\mathbf{\ss}}_{\mathbf{27}}*\mathbf{C}\mathbf{B}\mathbf{T}\mathbf{\hbox{-}}\\ {}\kern0.5em {\mathbf{I}}_{\mathbf{j}}*\mathbf{P}{\mathbf{A}}_{\mathbf{j}}*\mathbf{T}\mathbf{i}\mathbf{m}{\mathbf{e}}_{\mathbf{ij}}*\mathbf{I}\mathbf{S}\mathbf{P}\mathbf{j}+\\ {}\kern0.5em {\mathrm{\ss}}_{28}*\mathrm{C}\mathrm{B}\mathrm{T}\hbox{-} {\mathrm{I}}_{\mathrm{j}}*\mathrm{B}{\mathrm{W}}_{\mathrm{j}}\kern0.5em +\kern0.5em {\mathbf{\ss}}_{\mathbf{29}}*\mathbf{C}\mathbf{B}\mathbf{T}\mathbf{\hbox{-} }{\mathbf{I}}_{\mathbf{j}}*\mathbf{B}{\mathbf{W}}_{\mathbf{j}}*\mathbf{T}\mathbf{i}\mathbf{m}{\mathbf{e}}_{\mathbf{ij}}\kern0.5em +{\mathrm{\ss}}_{30}*\mathrm{C}\mathrm{B}\mathrm{T}\hbox{-} {\mathrm{I}}_{\mathrm{j}}*\mathrm{B}{\mathrm{W}}_{\mathrm{j}}*\mathrm{IS}{\mathrm{P}}_{\mathrm{j}}\kern0.5em +\kern0.5em {\mathbf{\ss}}_{\mathbf{31}}*\mathbf{C}\mathbf{B}\mathbf{T}\mathbf{\hbox{-}}\\ {}\kern0.5em {\mathbf{I}}_{\mathbf{j}}*\mathbf{B}{\mathbf{W}}_{\mathbf{j}}*\mathbf{T}\mathbf{i}\mathbf{m}{\mathbf{e}}_{\mathbf{ij}}*\mathbf{I}\mathbf{S}{\mathbf{P}}_{\mathbf{j}}\end{array} $$

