
In this regression equation, SE = sleep efficiency; ß_0ij_ = intercept; time denotes the post intervention (T1) versus baseline (T0) assessment week; CBT = cognitive behavior therapy assignment; BL = bright light assignment; PA = physical activity assignment; BW = body warming assignment; ISP = insomnia subtype probability; and ß_1_ to ß_31_ denote effect estimates. The effects and terms of interest are shown in bold font. For example, line 2 shows in bold font the overall treatment by time interaction effect **ß**_**8**_ of CBT-I versus waitlist and the moderation of this effect **ß**_**10**_ by one’s insomnia subtype probability. Lines 3 to 5 show the corresponding effect estimates for BL, PA and BW interventions, and lines 6 to 8 the for their interaction with CBT-I. For clarity, the regression equation shows only one of the four expected ISPs. Wald tests will be used to evaluate the significance of the effect estimates. Statistical significance is thresholded at p = 0.05. The simultaneous estimation of all effects of interest in a single regression model compensates for multiple comparisons. Mixed effect model analyses will be implemented in MLwiN (version 2.02, Centre for Multilevel Modelling, University of Bristol, Bristol, UK.) and (R: A language and evironment for statistical computing, R Foundation for Statistical Computing, Vienna, Austria.).

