### Power and sample size

#### Statistical power estimates

The statistical power of mixed effect regression models with seven repeated measures (diaries) both before and after intervention have been calculated according to the equations given by Twisk, page 280 [90], similar to those calculations made in a previous repeated measures RCT that we published [91]. Statistical power calculations on repeated measures require an estimate of the intraclass correlation coefficient (ICC, that is, within-subject). We estimated the ICC for the primary outcome measure of subjective sleep efficiency from the 9-day sleep diaries [67] that we recently assessed through the internet for 27 people suffering from insomnia according to an Insomnia Severity Index ≥10 [92]. In agreement with the robust observation that night-by-night sleep variability is an intrinsic part of the insomnia symptomatology (reviewed in [88]), we found only a moderate ICC of 0.27, supporting the use of repeated assessment of the primary outcome measure to increase statistical power of the design.

Given this moderate ICC of 0.27, seven pre-assessments at T0, and seven post-assessments at T1, the 160 completing participants provide a power 1-beta of 0.80 to allow for the detection, at a significance of alpha = 0.05, of even small to medium main effects of CBT-I (minimal detectable difference d = 0.27 standard deviations), of each of the three CTs (d = 0.31) and of their interaction with CBT-I (d = 0.41). The minimally detectable difference in the time by treatment interaction between any two types of CT is small to medium as well (d = 0.38).

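### Fitting all effects in one regression model does not compensate for multiple comparisons: 14 or more effects on the primary outcome are each tested at 0.05 with no control across the family

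*Protocol article*

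**What the plan says.** Under Outcome measures, the protocol article fixes one primary outcome and one interval: "The primary outcome measure is the change from week 0 to week 5 in subjective sleep efficiency derived from the sleep diary".

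Under Treatment effects and moderation estimates it gives a mixed model with coefficients ß1 to ß31 and says: "The effects and terms of interest are shown in bold font". The tests are set by "Wald tests will be used to evaluate the significance of the effect estimates" and "Statistical significance is thresholded at p = 0.05". Multiplicity is dealt with in one sentence: "The simultaneous estimation of all effects of interest in a single regression model compensates for multiple comparisons". The equation is abbreviated: "For clarity, the regression equation shows only one of the four expected ISPs". The model is reused throughout: "For each outcome measure, all effects will be estimated simultaneously in one single linear regression equation".

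Under Power and sample size, the 160 completers give 80% power "to allow for the detection, at a significance of alpha = 0.05" for the effects listed there. The article gives no adjusted level, testing order, omnibus gate or named primary contrast.

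**The concern.** Simultaneous estimation and simultaneous inference are different things. Putting all terms in one equation means that each estimate is conditional on the others. It does not alter the rejection threshold of any test or limit the number of chances to reject. The terms of interest are ordinary fixed coefficients, so no shrinkage argument can be made for them either.

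The article thus accepts that multiple comparisons need compensating, and then names a method that does not do it. A reader would take a p value below 0.05 on any bold term as already protected. The moderation terms multiply with the number of ISPs, and the Discussion puts subtype-specific treatment choice at the centre of the study's ultimate goal.

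**Working it through.** **1. Count of effects.** The bold terms in the displayed equation are:
- Treatment by time: ß8, ß11, ß14, ß17 (CBT-I, bright light BL, physical activity PA, body warming BW) and ß21, ß25, ß29 (CBT-I combined with each chronobiological treatment, CT). That is 7.
- Moderation of those seven by one ISP: ß10, ß13, ß16, ß19, ß23, ß27, ß31. That is 7.

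Total: 14. The ISPs are the probabilities of belonging to each of four classes, so they sum to 1 and at most three can enter a model with an intercept. The fuller model then has 7 + 7×3 = 28 terms.

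**2. The plan's own power figures.** These show which level the design assumes. With T = 7 diaries per period and ICC = 0.27 (Statistical power estimates),

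d = (z(1−α/2) + z(0.80)) × √[(1/n1 + 1/n2) × (1 + (T−1)×ICC)/T],

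where (1 + 6×0.27)/7 = 0.3743 and, at two-sided α = 0.05, the z sum is 1.960 + 0.842 = 2.802. Sidedness is not stated; two-sided is assumed because one-sided gives 0.24 for CBT-I, not 0.27. The group splits are inferred from the design.

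| Effect | n1/n2 | d computed | d stated |
|---|---|---|---|
| CBT-I | 80/80 | 0.271 | 0.27 |
| Each CT | 40/120 | 0.313 | 0.31 |
| CT × CBT-I | 20/140 | 0.410 | 0.41 |
| CT v CT | 40/40 | 0.383 | 0.38 |

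All four reproduce at an undivided 0.05, so the sample size makes no allowance for multiplicity.

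**3. Independence benchmark.** The chance of at least one false positive in m tests is 1 − 0.95^m: 30% for m = 7, 51% for m = 14, 76% for m = 28.

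**4. The joint model itself.** The coefficients are correlated, so the planned fixed effects were simulated with no true effect: subject change scores, 20 participants per cell, 10,000 runs per setting. The ISPs were drawn from a four-class Dirichlet(0.5) distribution, which is an assumption. In every setting the error rate per test stayed at about 5%. The chance of at least one false positive was:

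| Coding | 14 terms | 28 terms |
|---|---|---|
| 0/1, raw ISP | 33% | 47% |
| 0/1, centred ISP | 37% | 56% |
| Effect coding, centred ISP | 46–47% | 67% |

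For the seven treatment-by-time terms alone it was 21–28% across settings. Ranges reflect repeated runs. If joint estimation compensated as stated, these values would be near 5%.

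**5. Cost of a four-test Holm procedure.** The smallest Holm level is 0.05/4 = 0.0125, with z = 2.498. The z sum becomes 2.498 + 0.842 = 3.339, so the detectable d grows by 3.339/2.802 = 1.19: from 0.27 to about 0.32 for CBT-I and from 0.31 to about 0.37 for each CT. Power at a difference sized for 80% becomes Φ(2.802 − 2.498) = Φ(0.304) = 62%.

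**The case against.** Four objections have weight.

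- **Error is not uncontrolled in every sense.** A reader might infer that there is no error control at all. The documents do not support that: each test is held at 5%, and a single primary outcome and interval are fixed. What is missing is control across the effects within that outcome.
- **The independence figures are too high.** A reader might also take 51% or 76% as the error rate, or count 35 tests (7 + 7×4, giving 83%) because four ISPs are expected. The terms share data, reference groups and ISPs, so the independence figures are upper values. The 35-term model cannot be fitted in one equation, because the four probabilities sum to 1.
- **The family is partly a matter of choice.** The Objectives list separate questions, and whether distinct treatments compared with control need joint control is debated. That would be a defensible position, but the article does not take it. It claims a compensation instead. The objection bears on how large the family should be, not on whether the sentence is correct.
- **The moderation terms may be meant for estimation.** The Background calls the work a first step, and the Discussion speaks of expected outcomes for individual patients. One cannot say that a treatment protocol will rest on these significance tests alone. The article nevertheless assigns them Wald tests at 0.05.

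An unseen analysis plan does not answer the point. The article states a method, the method does not work, and a plan that followed it would carry the error forward.

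**Conclusion.** The concern holds as a wrong statement of method. Per-test error is 5%, and across the family it is not controlled. Under the global null, the chance of at least one false positive on the primary outcome is about 33–47% for the 14 displayed effects, roughly 47–67% for 28, and about 21–28% for the seven treatment-by-time terms. The spread comes from the choice of coding and centring, which the article does not state. The levels also rest on equal cells of 20 and on the assumed subtype distribution. Every value is at least four times 5%, so the conclusion does not depend on the exact setting. The documents require correction of the sentence and a prespecified confirmatory set. They do not dictate one particular ranking of the objectives.

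**What to change.** Delete the sentence and, before the treatment code is broken, state which effects are confirmatory. The article reports recruitment as ongoing and says the code is broken only once the dataset is final, so this can still be prespecified.

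One workable option:
- **Primary family:** the four time-by-treatment effects on sleep efficiency (CBT-I v waitlist; BL, PA and BW v placebo), tested with Holm at 0.05.
- **Definition of these effects:** marginal contrasts, or effect coding with centred ISPs. Under 0/1 coding with the interactions in the model, ß8 is the CBT-I effect in placebo-CT participants at ISP = 0, and ß11, ß14 and ß17 are effects under waitlist at ISP = 0. Holm on those raw coefficients would not test overall effects.
- **Subtype moderation:** one joint multi-degree-of-freedom Wald test per treatment, in place of a separate test per ISP.
- **All remaining terms:** reported as not adjusted for multiplicity.

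The investigators should decide how the combination and moderation objectives rank, since both are listed as objectives.

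The cost is more than wording. The power section should state that at the strictest Holm step, power at the stated differences falls from 80% to about 62%, and that the minimal detectable d rises from 0.27 to about 0.32 for CBT-I and from 0.31 to about 0.37 for each CT. Later Holm steps are less strict, so this is the worst case for the procedure.

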### Power and sample size

#### Statistical power estimates

The statistical power of mixed effect regression models with seven repeated measures (diaries) both before and after intervention have been calculated according to the equations given by Twisk, page 280 [90], similar to those calculations made in a previous repeated measures RCT that we published [91]. Statistical power calculations on repeated measures require an estimate of the intraclass correlation coefficient (ICC, that is, within-subject). We estimated the ICC for the primary outcome measure of subjective sleep efficiency from the 9-day sleep diaries [67] that we recently assessed through the internet for 27 people suffering from insomnia according to an Insomnia Severity Index ≥10 [92]. In agreement with the robust observation that night-by-night sleep variability is an intrinsic part of the insomnia symptomatology (reviewed in [88]), we found only a moderate ICC of 0.27, supporting the use of repeated assessment of the primary outcome measure to increase statistical power of the design.

Given this moderate ICC of 0.27, seven pre-assessments at T0, and seven post-assessments at T1, the 160 completing participants provide a power 1-beta of 0.80 to allow for the detection, at a significance of alpha = 0.05, of even small to medium main effects of CBT-I (minimal detectable difference d = 0.27 standard deviations), of each of the three CTs (d = 0.31) and of their interaction with CBT-I (d = 0.41). The minimally detectable difference in the time by treatment interaction between any two types of CT is small to medium as well (d = 0.38).

There is unfortunately no readily available methodology to estimate the minimally detectable moderation effects of continuous variables (insomnia subtype probabilities) on a time by treatment interaction effect on a continuous outcome variable (sleep efficiency). In order to obtain a conservative estimate of minimally detectable moderation effects, we can dichotomize the continuous insomnia subtype probability variable by means of a median split, effectively generating two equal groups. The design then becomes one of three factors, each with two levels: time (T1 versus T0), treatment group (Treated versus Untreated on the specific intervention) and insomnia subtype (high versus low probability) and provides the ratio of available data in the subgroup or interest relative to the other available data, to be used once more in the equations given by Twisk, page 280 [90]. According to this conservative approach of mapping the continuous insomnia subtype probabilities onto a dichotomous variable, the 160 completing participants provide a power 1-beta of 0.80 to allow for the detection, at a significance of alpha = 0.05: of a small to medium moderation effects of insomnia subtype (1) on the time by CBT-I treatment interaction (d = 0.31); (2) on the time by each CT treatment interaction (d = 0.41); and (3) on the difference in the time by treatment interaction between any two types of CT (d = 0.44). The smallest detectable moderation effect of insomnia subtype on the time by combined CBT-I and CT interaction is medium sized (d = 0.55). We follow the convention on effect size given by Cohen [93], who suggested consideration of an effect size d of about 0.2 as “small” and an effect size of about 0.5 as “medium.” With an estimated dropout of 10 %, we will recruit 180 volunteers. The expected 160 completers thus allow for the detection of small to medium effect sizes.

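### The stated detectable differences match a comparison of seven post-treatment nights only, not the pre-post treatment-by-time effect that the model tests; under the stated model the CBT-I figure is conservative

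*Protocol article*

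**What the plan says.** Under Statistical power estimates, the article describes power for mixed models with seven diaries before and seven after the intervention: "Given this moderate ICC of 0.27, seven pre-assessments at T0, and seven post-assessments at T1". On that basis, the planned completers are said to "provide a power 1-beta of 0.80" at the 5% level. The main effect for CBT-I is reported as a "minimal detectable difference d = 0.27 standard deviations". The corresponding values are 0.31 for each CT and 0.41 for CT combined with CBT-I (the interaction). A difference between two types of CT is given as d = 0.38 and is labelled a time-by-treatment interaction. The ICC of 0.27 comes from one 9-day diary series in 27 people, and the equations are attributed to a textbook page.

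Under Outcome measures, the primary outcome is the change in diary sleep efficiency from week 0 to week 5. Under Treatment effects and moderation estimates, "Mixed effect models will be applied to estimate all time by treatment effects". The model has two levels, with 14 nights nested within subjects. The CBT-I effect is the treatment-by-time coefficient (beta 8), judged by a Wald test, and "Statistical significance is thresholded at p = 0.05".

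**The concern.** The power statement and the planned test should refer to the same quantity. A difference in change between two weeks and a difference in one week's mean have different variances. The first depends on how strongly a person's week-0 level predicts the week-5 level; the second does not. If the printed figures come from a one-week formula, the 80% power attached to them is not the power of the primary test, and the reader cannot tell how far it is off. The only correlation in the calculation was estimated within a 9-day window, so it cannot describe how stable a person's level is across five weeks.

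**Working it through.** **Inputs.** From the article: 160 completers, alpha 0.05, power 0.80, ICC 0.27, seven nights per week of assessment, a 2 x 4 factorial. Assumed: equal allocation (80 per CBT-I level, 40 per CT level, 20 per cell), two-sided alpha, and d scaled by the total SD of a single night. The article does not state the sidedness or the SD, but these choices reproduce its figures.

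**Step 1: reproduce the stated figures.** The variance of one seven-night mean, in units of the single-night variance, is V = (1 + 6 x 0.27)/7 = 0.3743. With (1.960 + 0.842)^2 = 7.849, the detectable difference is d = sqrt(7.849 x V x (1/n1 + 1/n2)).

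| Contrast | n1 v n2 | Computed | Stated |
|---|---|---|---|
| CBT-I | 80 v 80 | 0.271 | 0.27 |
| Each CT | 40 v 120 | 0.313 | 0.31 |
| CT v CT | 40 v 40 | 0.383 | 0.38 |
| CT x CBT-I | 20 v 140 | 0.410 | 0.41 |

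The moderation figures follow the same pattern: 0.313, 0.410, 0.443 and 0.560 against the stated 0.31, 0.41, 0.44 and 0.55. Seven of the eight agree to two decimals and the last is within 0.01. For CBT-I the alternatives do not fit: 14 nights as one series gives 0.251, a one-sided alpha gives 0.240, and a 7 + 7 change with the single ICC gives 0.202.

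**Step 2: the planned contrast under the stated model.** With a subject intercept only, two nights of one person correlate 0.27 whether they fall in the same week or not. The variance of the change in weekly means is then 2 x (1 - 0.27)/7 = 0.2086. For 80 v 80, d = sqrt(7.849 x 0.2086 x 2/80) = 0.202, and power at d = 0.27 is 0.96.

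**Step 3: underlying level not fully stable.** Let r be the correlation of a person's underlying level between weeks 0 and 5. The article gives no value, so everything here for r below 1 is an assumption. The change variance is 2(V - 0.27r), which equals V at r = 0.3743/(2 x 0.27) = 0.693. For a test that uses this variance, 80 v 80:

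| r | Change variance | Detectable d | Power at d = 0.27 |
|---|---|---|---|
| 1 | 0.2086 | 0.20 | 0.96 |
| 0.9 | 0.2626 | 0.23 | 0.92 |
| 0.69 | 0.374 | 0.27 | 0.80 |
| 0.5 | 0.4786 | 0.31 | 0.69 |

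**Step 4: the same situation with a random intercept only.** Such a model pools the week-to-week variation of persons into its residual. At r = 0.5, each person contributes 12 within-week degrees of freedom with expectation 0.73 and one between-week degree with expectation 3.5 x 0.4786 = 1.675. The residual averages (12 x 0.73 + 1.675)/13 = 0.803. The model then takes the change variance to be 2 x 0.803/7 = 0.229, when it is 0.479. The critical value on the true scale falls from 1.96 to 1.96 x sqrt(0.229/0.479) = 1.36, so the two-sided type I error is about 0.17 and the rejection rate at d = 0.27 is about 0.87. Simulation of this test gave the same values.

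**Step 5: adjustment for the week-0 mean.** The variance becomes V(1 - (0.27r/V)^2). For 80 v 80 the detectable d is 0.19 at r = 1, 0.23 at r = 0.7, 0.25 at r = 0.5 and 0.27 at r = 0.

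**The case against.** The strongest reply is that the figure errs on the safe side. The article specifies two levels and one ICC, which means r = 1, and then 0.27 understates what the trial can detect. That stands, and it governs how the point should be read.

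A reader might infer that the trial is underpowered, or that the planned test has power of only 0.69 at r = 0.5. The documents support neither. No value of r is given, and the 0.69 belongs to a valid test of change. The random-intercept Wald test would reject more often, about 0.87, but at the price of false positives. If r is below 1, the problem with the test as described is therefore its type I error.

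Three further reservations hold in part. The textbook page is not at hand, so the post-only origin is inferred from the numerical match; agreement on this scale across eight figures is hard to put down to chance. The article calls the 0.27 and 0.31 figures main effects, but the same sentence invokes the pre-treatment nights, and the effects of interest in the model are treatment-by-time terms. Finally, 80 v 80 may not be what beta 8 estimates. With 0/1 indicators and the CBT-I x CT x time terms in the model, beta 8 would be CBT-I v waitlist within placebo CT, 20 v 20. Its detectable d is then sqrt(7.849 x 0.2086 x 2/20) = 0.40 even at r = 1, ignoring subtype terms. The article calls the effect overall and does not state the coding, so this is unresolved.

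An article may leave a sensitivity range to a fuller document. Here, however, the inputs, the result and the model are all stated, and they do not agree.

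**Conclusion.** The point holds as a mismatch between the power statement and the planned test. The stated detectable differences are those of a post-only comparison of seven-night means, although the text counts the baseline nights and the test is on change.

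Under the stated two-level model the error is on the conservative side for an overall 80 v 80 CBT-I contrast: about 0.20 rather than 0.27, and power of about 0.96 rather than 0.80 at d = 0.27. An error in the other direction needs r below about 0.69 and a valid test of change, and the documents neither give nor exclude such a value. No shortfall in sample size is shown. The conclusion rests on equal allocation, two-sided alpha, d in single-night SD units, and the inference from the numerical match. It should be corrected because the printed power does not describe the primary test, and because the single-ICC model on which the favourable reading depends is itself untested across five weeks.

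**What to change.** Restate the detectable differences for the treatment-by-time contrasts actually tested, over a stated range of r such as 0.5, 0.7, 0.9 and 1. Name the SD that scales d and the coding of the treatment indicators, so that it is clear whether the CBT-I effect is overall or within placebo CT.

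Preferably, also analyse the week-5 nights adjusted for the person's week-0 mean, or constrain the baseline means to be equal across limbs and include a subject-by-week random term. The detectable difference for an overall 80 v 80 CBT-I contrast then lies between 0.19 and 0.27 for r from 1 to 0, so the printed 0.27 becomes an upper bound. That assurance does not extend to a CBT-I effect within placebo CT (20 v 20).

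The cost is a recalculated table and a small change in the model wording. No extra participants or data are needed, since the week-0 diaries are already collected. The article reports recruitment as ongoing with 60 participants through the protocol, and treatment codes stay closed until the dataset is final, so the change can be made before unblinding.
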